#### Inclusion criteria

In the epidemiological study, participants will be patients that meet the following inclusion criteria (see Fig. 1):
Being hospitalized in the acute geriatrics department of a French university hospital where the study is conductedHaving expressed opposition to diagnostic or therapeutic procedures, as defined aboveNot expressly objecting to the collection of personal data

**Fig. 1 Fig1:**
[figure not shown]
Inclusion flow diagram

For the comprehensive (qualitative) part, the inclusion criteria include patients, carers, and relatives who:
Signed an informed consent formCan participate in a semi-directive interview with the researcher (the Mini-Mental States > 10, no phasic disorders)

Patients under legal protection are considered vulnerable. Their dependency is higher, and fundamental decisions concerning their care are most often taken by substitutes. However, these patients can still express opposition to care in various ways. Since they are under legal protection, listening to the expression of their will allows a better understanding of their precarious condition. As such, their integration into the research protocol is necessary. A specific information and consent form will be presented to the patient and guardian, and both consents will be obtained.

As this study will be a pilot study, we will include patients with all forms of cognitive status. More specific studies should be developed in the future.

#### Exclusion criteria

For the epidemiological part, patients will be excluded if they explicitly oppose the use of their health data.

For the comprehensive (qualitative) part, the following exclusion criteria will be used:
Patient with severe neuro-cognitive disorders [33, 34] already known or diagnosed at service entry (MMS < 10) or inability to take part in a semi-directive interview (e.g., phasic disorders)Opposition to care that is not explicit or provided by a third partyRefusal to participate in the study

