However, even though the question of oppositional behaviors has been at the heart of many conceptual works in the field of geronto-psychiatry for more than 30 years, its study in clinical situations, and in particular during short hospital stays, remains rare. Indeed, conceptual approaches have used the prism of person-centered care to address the limitations of the care plan. In acute care, older patients may behave in opposition to medical strategies, even though the objective deployed corresponds to the patient’s previous personalized care plan. The technical nature of the treatment may lead the patient to oppose its implementation, particularly in cases of neurocognitive disorders. As such, the question of patients’ opposition to diagnostic or therapeutic proposals is a recurring issue faced by medical and paramedical teams. How can we explore the meaning of this opposition, when, paradoxically, it does not seem nameable, at first glance, by the patient? It is essential for carers and doctors, but also for relatives, who are often at the forefront of delegated decision-making processes [25], to obtain explanatory elements on this question to better position themselves and find the right balance between patients’ right to autonomy and the need to intervene to preserve his/her health.

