A quantitative study seems necessary to quantify and better understand the parameters associated with situations involving opposition to diagnostic and therapeutic procedures. Although these events are often mentioned in medical literature, they are not documented or compiled in hospital records. Epidemiological studies must be associated with qualitative and comprehensive analyses of events to ensure an in-depth understanding of the opposition expressed by older patients. Is this opposition linked to a distorted and negative representation by patients of the proposed diagnostic or therapeutic procedure? In older people with a certain degree of delirium and/or cognitive deterioration, treatment may be perceived as a threat, intrusion, coercion, obstruction, violence, or even aggression. It is therefore conceivable that some intrusive procedures may be refused. Is this opposition an expression of a desire to control one’s own life until death? Is it not the ultimate expression of the existence of oneself, the expression of an ability to decide for and by oneself, in a world characterized by several constraints and dependence for all acts of daily life? Is this opposition expressing a feeling of indignity experienced in a societal context, or a reaction to ageist tendencies [28, 29] that can generate a sense of social uselessness among the older population? The qualitative component of the present study also contributes to the exploration of interactions between doctors, carers, and relatives confronted with patient opposition; the functioning of collegial meetings and decision-making methods are also addressed to better understand some consequences of the dilemma that arises in cases of opposition to diagnostic or treatment in older patients.

In order to answer these questions and verify the aforementioned hypotheses, it is necessary, in view of the specificities of opposition to medical care and target population (older people, including persons with neurocognitive disorders), to carry out a pilot study beforehand, with the following specific objectives:
To verify the applicability of the proposed definition of opposition to medical care and its reproducibilityIdentify the proportion of patients expressing opposition to medical care according to the proposed definitionIdentify the key elements to be included in the qualitative interview, based on a preliminary interview grid.

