### Study objectives

Epidemiological component: In the epidemiological survey, the objective will be to identify and establish the frequency of situations in which patients will express opposition to treatment or diagnostic procedures. The data will be obtained in the acute geriatric ward of a French university hospital, over 1 year.Comprehensive component: During the semi-structured interviews with carers and relatives involved in the epidemiological component, the objective will be to identify, describe, and understand the meaning of the opposition to treatment or diagnostic procedures expressed by patients included in the study (see below).

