#### Epidemiological component

When patients will present opposition to a diagnostic or therapeutic procedure, they will be included in the epidemiological component of this study by the attending physician. The physician will complete a data collection form to initiate the patient’s participation in the study. This form covers the patient’s general demographic and medico-social data. It focuses on the information related to the opposition that had occurred (drugs, procedures) and on the circumstances of the opposition (e.g., organ failure, sepsis, delirium). This survey will also be completed at discharge, to describe the outcomes resulting from this opposition (respect or not for the patient’s position, healthcare strategy, mortality).

The data collected are detailed below, in the “Data analysis” section.

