### Data collection strategies

#### Recruitment

This study aims to investigate opposition situations. To make a rigorous analysis, it seems necessary to do an exhaustive census of opposition situations. In that way, we will quantify the number of situations in which there is opposition to diagnostic or therapeutic procedures handled in the department for 1 year.

Given the population and the subject of this study, it is foreseeable that opposition to participation will occur, even though our focus on the refusal and thus the interest and respect for the person’s will can facilitate exchanges. This concern justifies the extension of the comprehensive study for an additional year and a half.

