#### Epidemiological component

The medical and medico-social data used for the quantitative component will be compiled in a standard electronic form. The data will be collected during the consultation of the patients’ usual medical records including H24 daily notes from medical, nurses, and auxiliary nurses.

To characterize the population under study, the following data will be used:
Demographic characteristics of patients (age, gender)Medical data of patients that are generally collected at the time of their admission (history, usual medications, nutritional, cognitive, motor, thymic status)Medico-social data relevant to the standardized geriatric assessment usually carried out in the service (capacity to perform activities of daily living, instrumental activities of daily living, place, way of life, presence of family and relatives, home-support workers)

To define oppositional behaviors, the following data will be collected:
Circumstances of the opposition (who notices it, when, who reports it in the care record, recurrence of the event)Patient’s oppositional attitude (oral argumentation, physical opposition, catheter removal, type, duration)The target of opposition (single clinical element or overall attitude of catheter withdrawal and refusal of the procedure, taking medication, etc.), medication (molecule, route of administration), and/or material (venous, nasogastric, or urinary catheter) that triggered patients’ oppositionMedical circumstances (organ failure, sepsis, delirium, etc.) surrounding the refusal of diagnostic or therapeutic procedures

To better understand the consequences of the opposition behavior, the following data will be collected:
Medical decisions about the diagnosis or therapeutic strategies (continuation despite patient’s opposition or acceptance of patient’s opposition and change of medical orientation)The organization of the collegial meeting and the reasons involvedPatients’ outcomes following the opposition behavior (discharge, transfer to another unit, death)

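### The count described as an exhaustive census can only be a minimum: opposing patients who object to data use leave the numerator, and the attending physician is the only case finder described

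*Protocol article*

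**What the plan says.** In the protocol article, Study objectives states for the epidemiological survey that "the objective will be to identify and establish the frequency of situations in which patients will express opposition to treatment or diagnostic procedures", in one acute geriatric ward over one year. Hypotheses lists the proportion of opposing patients among the specific pilot objectives. Recruitment sets the standard of completeness: "it seems necessary to do an exhaustive census of opposition situations".

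Three provisions govern who is counted:

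- *Exclusion criteria*, epidemiological part: "patients will be excluded if they explicitly oppose the use of their health data". Inclusion criteria gives the same rule in positive form.
- *Experimental planning, Epidemiological component*: when patients oppose a procedure, "they will be included in the epidemiological component of this study by the attending physician", who completes the form that starts participation.
- *Definition of opposition*: a case needs repeated, explicit opposition met by two or more different people. Refusals that belong to a free and informed choice are left out.

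The data themselves come from "usual medical records including H24 daily notes from medical, nurses, and auxiliary nurses" (Data collection strategies, Epidemiological component). The Discussion acknowledges as a limitation that the study works from medical traces, but does not connect this with undercounting. Study status reports 33 situations after 20 months, 5 of them in the interview part.

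**The concern.** The protocol's own standard is completeness, but its entry rules cannot deliver it. The data-use rule removes from the numerator only people who already meet the definition of opposition. The physician route adds a second loss: the definition requires a pattern seen by more than one person, and one doctor has to piece that pattern together before the case exists for the study. Neither loss is measured in the text that is visible.

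Frequency is one of the results the pilot is meant to deliver, and the Discussion intends the findings for practice and training. A reader told that the census was exhaustive would take the figure as the burden of opposition on the ward, when it is the part of that burden that was notified and not objected to.

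**Working it through.** **Nothing to reproduce.** The article states no expected frequency, precision or sample size for the survey. What can be checked is the direction of the error and, under stated assumptions, its possible size.

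**Direction.** Let x be the true number of opposing patients among N admissions, and a the number excluded or not notified. The observed proportion is (x − a)/N, or (x − a)/(N − a) if those patients also leave the denominator. The first is below x/N whenever a > 0. The second is below x/N whenever N(x − a) < x(N − a), that is, whenever a > 0 and x < N. The direction therefore does not depend on how the denominator is handled.

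**Recorded yield in the census year.** Inputs: 33 situations, 5 of them in the interview part (Study status); 54 beds, and after the first year additions only through the interview part (Population and duration of the study); 60 patients seen in one month (Statistical analysis of epidemiological data). If that plan was followed, at most 5 of the 33 arose after month 12, so 33 − 5 = 28 to 33 belong to the census year.

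- Per patient-day, assuming 90% occupancy: 54 × 0.9 × 365 = 17,739 patient-days. 28/17.739 = 1.6 and 33/17.739 = 1.9 per 1000, or one situation every 365/33 = 11 to 365/28 = 13 days.
- Per patient, assuming 60 a month throughout and one situation per patient: 12 × 60 = 720. 28/720 = 3.9% and 33/720 = 4.6% (exact 95% interval for 33/720: 3.2% to 6.4%).

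**What a shortfall would do.** True count = recorded count / capture fraction. For 33 recorded on the base of 720:

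| Assumed share missed | True count | True proportion |
|---|---|---|
| 10% | 36.7 | 5.1% |
| 20% | 41.2 | 5.7% |
| 30% | 47.1 | 6.5% |
| 50% | 66.0 | 9.2% |

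A shortfall of about 1 − 4.58/6.38 = 28% would put the true value above the upper confidence limit. Also dropping the missed patients from the denominator moves the observed 4.58% only to between 4.61% (10% missed) and 4.80% (50% missed).

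**Both losses together.** Capture = (1 − objection rate) × notification rate. With 5% objecting and 90% notified, capture is 0.95 × 0.90 = 0.855 and 33/0.855 = 38.6. With 10% and 70% it is 0.63, giving 52.4. With 20% and 50% it is 0.40, giving 82.5. None of these rates is in the documents; they show a range and estimate nothing.

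**The case against.** The strongest reply is that the study was built to overcome poor recording. A reader might infer a contradiction from Hypotheses, which says of these events that "they are not documented or compiled in hospital records". That sentence describes practice before the study and is the reason given for doing it. The study adds a prospective physician form and draws on round-the-clock notes that include nurses and auxiliary nurses. This stands: the records statement does not show that the study's own ascertainment fails. It does not remove the dependence on the physician to start a case.

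Four other stronger readings also lack support:

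- *Expected refusal.* Recruitment says "it is foreseeable that opposition to participation will occur", but uses this to justify extending the interview part, which needs signed consent. It gives no objection rate for the survey.
- *Who is missed.* That the missing patients are the most oppositional, or that the events happen mainly at night, is stated nowhere. Objecting to data use is a different act from the opposition defined; that the two go together is plausible but not shown.
- *Low yield as proof.* Dividing 33 situations by 20 months of patient-days (54 × 0.9 × 30.4 × 20 = 29,549) gives 1.1 per 1000, which looks low for what Background calls "a recurring issue faced by medical and paramedical teams". But the census lasts 12 months, and the definition is much narrower than opposition in general.
- *Net bias.* An informed refusal wrongly counted as opposition would push the figure up. The downward direction is certain only for the two losses named.

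It is also fair that excluding objectors respects their choice and may be legally required, that exhaustiveness is worded as an aim, and that the flow diagram or the full protocol may hold a count of objectors. These points limit the criticism to how the result is counted and labelled. They do not make the count complete.

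**Conclusion.** The point holds in a limited form. The entry rules yield a minimum frequency, while the stated standard is an exhaustive census. The direction follows from the rules alone for the two named losses. The size is unknown, because the documents give neither an objection rate nor a notification rate. Under the assumed ranges, 33 recorded situations could stand for 39 to 83, and on the 720-patient base a shortfall of about 28% would already exceed the sampling uncertainty. The yield of about 1.6 to 1.9 per 1000 patient-days rests on 90% occupancy and on later entries coming only through the interview part. It does not show under-capture: as described, the design cannot separate a rare event from a missed one. The change is worth making because it alters what the pilot may conclude about frequency.

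**What to change.** 1. Keep a non-identifying count of patients who met the definition of opposition but objected to data use. Recruitment began in January 2018 and Study status is written at 20 months, so for the elapsed census year the count should be recovered where possible and its gaps stated. Report the frequency with and without these patients, on a stated denominator.
2. Where data access permits, take a sample of weeks from the census year and compare the 24-hour physician, nurse and auxiliary-nurse notes with the physician forms. Report the percentage of qualifying situations found in the notes that had been notified. Do not turn this into a two-source Chapman estimate: the notes are already the study's data source and are not independent of the forms. Access to the notes of patients not included must be confirmed first, as the article does not state it.
3. If the second step is not done, call the result a minimum notified frequency wherever it is reported, and drop the description as an exhaustive census.

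The cost is a simple tally, some note review for the second step, and a less favourable label for the result. The third step costs only wording.

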### Experimental planning (see Fig. 2)

The time of the opposition, as defined above, corresponds to D0.

**Fig. 2 Fig2:**
[figure not shown]
Experimental planning

#### Epidemiological component

When patients will present opposition to a diagnostic or therapeutic procedure, they will be included in the epidemiological component of this study by the attending physician. The physician will complete a data collection form to initiate the patient’s participation in the study. This form covers the patient’s general demographic and medico-social data. It focuses on the information related to the opposition that had occurred (drugs, procedures) and on the circumstances of the opposition (e.g., organ failure, sepsis, delirium). This survey will also be completed at discharge, to describe the outcomes resulting from this opposition (respect or not for the patient’s position, healthcare strategy, mortality).

The data collected are detailed below, in the “Data analysis” section.

#### Comprehensive part

Among patients presenting an opposition, we will select about ten situations that will be included in the comprehensive part of the study, to explore these situations through qualitative methodological tools (interviews, surveys, and observations). All epidemiological data will also be collected for these patients.

Thus, a comprehensive data collection will be conducted as follows:
A semi-directed interview will be carried out with the patient, a relative designated by the patient, and the usual carer at home or the healthcare institution. These interviews (3 per situation) will be conducted by a researcher, a psychologist, or a sociologist (the complementarity of the two scientific disciplines allows triangulation of data collected in the various interviews), according to a pre-established interview framework (see Table 1).Medical questionnaire for the general practitioner (1 per situation). The qualitative medical form will be completed by the investigating physician during a telephone call with the family physician.As soon as the opposite situation leads to difficulties in medical care, and as soon as the setting up of collegial meetings will be organized, these meetings (at least 1 per situation) will also be attended by a psychologist and a sociologist of the research team. They will use an observation matrix to describe the content of collegial meetings, as observers (non-participants) in the discussion*.*

**Table 1 Tab1:** Themes to be used during semi-structured interviews

Themes to be used during semi-structured interviews	
**History of care**	History of hospitalization
	Medical decisions
**Relationship with the caregiver**	Precedence of medical decisions
	Relationship with health professionals
**Home living/medicalization**	Relatives
	Home carer
	General practitioner
	Dependency
**Representation**	Previous experience with the illness, hospitalizations, treatments, operations

About 10 patients will be included in the comprehensive study. The sample could be re-evaluated if there is no data saturation, or if there are some difficulties to collect data because of patients’ cognitive status.

The verbatims will be analyzed according to the principles of the grounded theory (see below).

### Data collection strategies

#### Recruitment

This study aims to investigate opposition situations. To make a rigorous analysis, it seems necessary to do an exhaustive census of opposition situations. In that way, we will quantify the number of situations in which there is opposition to diagnostic or therapeutic procedures handled in the department for 1 year.

Given the population and the subject of this study, it is foreseeable that opposition to participation will occur, even though our focus on the refusal and thus the interest and respect for the person’s will can facilitate exchanges. This concern justifies the extension of the comprehensive study for an additional year and a half.

#### Epidemiological component

The medical and medico-social data used for the quantitative component will be compiled in a standard electronic form. The data will be collected during the consultation of the patients’ usual medical records including H24 daily notes from medical, nurses, and auxiliary nurses.

To characterize the population under study, the following data will be used:
Demographic characteristics of patients (age, gender)Medical data of patients that are generally collected at the time of their admission (history, usual medications, nutritional, cognitive, motor, thymic status)Medico-social data relevant to the standardized geriatric assessment usually carried out in the service (capacity to perform activities of daily living, instrumental activities of daily living, place, way of life, presence of family and relatives, home-support workers)

To define oppositional behaviors, the following data will be collected:
Circumstances of the opposition (who notices it, when, who reports it in the care record, recurrence of the event)Patient’s oppositional attitude (oral argumentation, physical opposition, catheter removal, type, duration)The target of opposition (single clinical element or overall attitude of catheter withdrawal and refusal of the procedure, taking medication, etc.), medication (molecule, route of administration), and/or material (venous, nasogastric, or urinary catheter) that triggered patients’ oppositionMedical circumstances (organ failure, sepsis, delirium, etc.) surrounding the refusal of diagnostic or therapeutic procedures

To better understand the consequences of the opposition behavior, the following data will be collected:
Medical decisions about the diagnosis or therapeutic strategies (continuation despite patient’s opposition or acceptance of patient’s opposition and change of medical orientation)The organization of the collegial meeting and the reasons involvedPatients’ outcomes following the opposition behavior (discharge, transfer to another unit, death)

